# A quasi-randomised controlled trial of online distribution of home-based hepatitis C self-testing for key populations in Malaysia: a study protocol

**DOI:** 10.1186/s13063-022-06230-y

**Published:** 2022-04-12

**Keywords:** Hepatitis C, Self-testing, Key populations, Malaysia, Testing uptake, Linkage to care

## Abstract

**Background:**

Malaysia has an estimated hepatitis C virus (HCV) prevalence of 1.9% among its adult population and a history of providing HCV treatment in the public sector. In 2019, Malaysia launched a 5-year national strategic plan for viral hepatitis control and has been expanding HCV testing and treatment to the primary care and community levels, while actively engaging key populations in services for hepatitis care. The Ministry of Health (MoH) is seeking to specifically understand how to better target HCV services at men who have sex with men (MSM); HCV self-testing could increase the uptake of HCV testing among this group.

**Methods:**

We aim to integrate HCV antibody self-testing into an existing online platform used for HIV self-testing, to evaluate the acceptability and impact of an online HCV self-testing programme in Malaysia. This is a non-blinded parallel group quasi-randomised superiority study comparing HCV self-testing via an online distribution model with the standard care, which involves attending a clinic for facility-based HCV antibody testing (control, 2:1). Participants will be randomised to either the HCV self-testing via online distribution arm, in which either an oral fluid- or blood-based HCV self-test kit will be mailed to them, or the control arm, where they will be provided with information about the nearest centre with HCV testing. The primary outcome is the number and proportion of participants who report completion of testing. Secondary outcomes include the number and proportion of participants who (a) receive a positive result and are made aware of their status, (b) are referred to and complete HCV RNA confirmatory testing, and (c) start treatment. Acceptability, feasibility, attitudes around HCV testing, and cost will also be evaluated. The target sample size is 750 participants.

**Discussion:**

This study is one of the first in the world to explore the real-world impact of HCV self-testing on key populations using online platforms and compare this with standard HCV testing services. The outcomes of this study will provide critical evidence about testing uptake, linkage to care, acceptability, and any social harms that may emerge due to HCV self-testing.

**Trial registration:**

ClinicalTrials.gov NCT04982718

**Supplementary Information:**

The online version contains supplementary material available at 10.1186/s13063-022-06230-y.

## Administrative information

Note: The numbers in curly brackets in this protocol refer to SPIRIT checklist item numbers. The order of the items has been modified to group similar items (see http://www.equator-network.org/reporting-guidelines/spirit-2013-statement-defining-standard-protocol-items-for-clinical-trials/).

## Introduction

### Background and rationale {6a}

Globally, only 21% of the estimated 58 million people living with hepatitis C virus (HCV) know their HCV status [1]. To achieve the 2030 World Health Organization (WHO) global goals for hepatitis elimination, a significant scale-up of testing for hepatitis is needed [2]. HCV self-testing (referring to serological testing for HCV antibodies) could be a valuable tool that contributes to this scale-up of testing. WHO recently produced the first-ever recommendations on HCV self-testing [3]. These recommendations leveraged the large evidence base that has accumulated on the value of HIV self-testing as well as data from various studies on the feasibility, acceptability and values and preferences around HCV self-testing [4–8]. This evidence base demonstrates that people are able to correctly perform and interpret the results of an HCV self-test and that HCV self-testing is feasible and acceptable to end-users. The new WHO recommendations do note, however, that information is needed about how HCV self-testing impacts the uptake of HCV testing and linkage to care and how it is best delivered.

Self-testing for HIV has been shown to increase testing rates and acceptability in diverse populations around the world, in large part due to its convenience and privacy advantages [9]. However, the health systems in place for HIV are much more extensive than those which currently exist for HCV. Whereas testing and treatment for HIV are widely available through the public sector globally, the number of countries that currently provide HCV testing and treatment remains relatively limited. There is therefore a need to build an evidence base for the impact of HCV self-testing that includes data relating to uptake, linkage to care, and acceptability, as well as to capture information about any social harms that may emerge due to the use of HCV self-testing.

Malaysia has an estimated HCV prevalence of 1.9% among its adult population according to an opt-in screening campaign conducted in 2019 [10] and has a history of providing hepatitis C treatment in the public sector [11]. In 2019, Malaysia launched a 5-year national strategic plan for viral hepatitis control [12], and the country has been expanding HCV testing and treatment access to the primary care and community levels while actively engaging key populations in services for hepatitis care [11]. One group that the Malaysian Ministry of Health (MoH) would like to understand how to reach more effectively is men who have sex with men (MSM). Malaysia has a strong network of primary health clinics, which serve a large percentage of the population. However, due to considerable socioreligious stigma in Malaysia, MSM may be less likely than other population groups to regularly attend primary health services and therefore represent good candidates for HCV self-testing [13]. To explore the usefulness of HIV self-testing in Malaysia to reach key populations such as MSM, a pilot study offering HIV self-testing via an online platform (JomTest) was launched in November 2020, in partnership with the Malaysian AIDS Council (MAC) and the University of Malaya [14]. JomTest caters to people who identify as MSM, people who inject/use drugs (PWI/UD), transgender women, sex workers and persons engaging sex workers. These same groups may also be at high risk of contracting HCV; however, estimates for HCV prevalence among these groups in Malaysia are currently limited.

In the present study, we will integrate HCV self-testing with the existing online HIV self-testing platform, JomTest. We aim to evaluate the impact, acceptability, feasibility and cost of home-based HCV self-testing made accessible via an online platform in Malaysia.

### Objectives {7}

The primary objective of this study is to assess the impact of home-based HCV self-testing offered via an online platform on the uptake of HCV antibody testing among key populations. The secondary objectives of the study are as follows:
To assess the impact of HCV self-testing on the number of HCV antibody-positive individuals who are aware of their HCV statusTo assess the impact of HCV self-testing on linkage to care and completion of HCV RNA confirmatory testing among HCV antibody-positive individualsTo assess the impact of HCV self-testing on treatment initiation in HCV RNA-positive individuals eligible to begin treatmentTo assess the acceptability and feasibility of HCV self-testing at baseline and after study participationTo compare the cost of HCV self-testing with the cost of standard of care

### Trial design {8}

This is a parallel-group non-blinded superiority study comparing HCV self-testing via an online distribution model on the JomTest platform with the standard of care (control). The participant allocation ratio will be 2:1. Participants in the control group will be offered an HCV self-test if they do not go to a primary healthcare clinic for facility-based testing after the completion of two follow-up surveys.

## Methods: participants, interventions and outcomes

### Study setting {9}

This study will be performed nationwide across Malaysia. Due to the home-based nature of self-testing, there are no intervention sites. Participants in the control group will be directed to their nearest clinic that offers facility-based HCV testing.

### Eligibility criteria {10}

Participants are only eligible to be included in the study if all of the following inclusion criteria are met:
*Age* ≥ 18 years*Eligible to access services on the JomTest online platform**Able to read and understand Bahasa Malaysia or English**Able to understand the scope of the study and provide written informed consent*Not tested for HCV within the last 6 months

Participants are excluded from the study if they s*elf-report a previously confirmed, positive HCV status (either antibody or RNA test).*

### Who will take informed consent? {26a}

The consenting process will be performed via the online platform. An online form will explain the nature of the study to prospective participants. A hotline will also be available to provide answers to any questions about the study.

Participants will only be able to advance to the next step of the study on the online platform once they have completed the online informed consent form.

### Additional consent provisions for collection and use of participant data and biological specimens {26b}

Not applicable, as this study will not be collecting or using biological specimens.

### Interventions

#### Explanation for the choice of comparators {6b}

As this study is intended to demonstrate the superiority of HCV self-testing compared with the standard of care facility-based testing, this was chosen as the comparator.

#### Intervention description {11a}

Participants will be randomised to the intervention or control groups in a 2:1 ratio. In the intervention group, participants will receive an HCV self-test kit delivered in non-identifiable packaging to their home or a preferred mailing address. The kit will include the test itself, instructions for use, additional supporting materials and information on how to access a live chat facility and a call centre in case they have any questions about the test. To evaluate the two sampling methods for HCV self-testing, the first 250 participants in the intervention group will receive an oral fluid-based HCV self-test, and the next 250 participants will receive a blood-based fingerstick HCV self-test. For the oral fluid-based test, participants must swab their upper and lower gums with the test device, place it in the tube provided and read the results within 20 to 40 min of taking the test. For the blood-based test, participants must collect a drop of blood by pricking a finger with a lancet, transfer the blood onto the test device, add the diluent and read the results after 15 min. Participants will be invited to conduct the HCV self-test and then report back if they completed the test as well as enter the test results via the online platform.

In the control group, participants will receive information about the standard of care HCV antibody testing available at local testing sites in their community and information about additional supporting materials, such as access to the live chat facility and the call centre for any questions about testing. At local testing sites, HCV testing involves obtaining blood via a finger prick or obtaining blood from the arm.

As there is currently no quality-assured HCV self-test available, the professional-use OraQuick® HCV Rapid Antibody Test and First Response® HCV Card Test, which have been adapted by the manufacturers for self-testing by being repackaged and labelled with instructions for use, will be used in this study. The OraQuick® HCV Rapid Antibody Test is prequalified by WHO and CE-marked for professional use (sensitivity 98.1%, specificity 99.6%); the First Response® HCV Card Test is CE-marked and currently under WHO review for professional use (sensitivity 100%, specificity 100%). Neither of these professional-use tests are yet registered with the Medical Device Authority in Malaysia. The OraQuick® HCV Self-Test and First Response® HCV Self-Test kits provided to participants in the intervention group will be labelled for Research Use Only (RUO). For these reasons, HCV self-testing results from this study will not be used for clinical decision making, and all participants who report a positive HCV self-test and who report to a clinic will receive follow-up HCV rapid testing in the clinic.

#### Criteria for discontinuing or modifying allocated interventions {11b}

This is not applicable for this study given its design.

#### Strategies to improve adherence to interventions {11c}

Participants will be provided with several supporting tools to minimise the rate of errors in the self-testing process and any possible confusion in the interpretation of the test results. Printed instructions for use in English and Bahasa Malaysia will be delivered along with the test kit; pictorial guides on how to use the test will also be included. Participants will also be provided with a link to a video guide and have access to a live chat facility and a call centre.

#### Relevant concomitant care permitted or prohibited during the trial {11d}

There is no concomitant care prohibited during the study.

#### Provisions for post-trial care {30}

Participants who are HCV antibody-negative will be encouraged to seek retesting at a later date, as per the recommended testing frequencies for key populations of the Malaysian national HCV algorithm. Any participants found to be HCV antibody-positive through the study will be supported to access HCV management and care services for further HCV testing and HCV treatment, as required by the national HCV programme. Participants will also be provided with additional assistance to facilitate linkage to care through MAC’s existing peer navigation system, as outlined in the organisation’s standard operating procedures.

### Outcomes {12}

The primary outcomes are the number and proportion of participants who report completing HCV antibody testing in the intervention group and to assess whether the proportion of participants who report completing HCV antibody testing in the intervention group is greater than that of the participants in the control group by a margin of 20%.

The secondary outcome measures are as follows: the number and proportion of HCV antibody-positive individuals made aware of their HCV status in the intervention versus the control groups. The number and proportion of HCV antibody-positive individuals who are referred to and complete HCV RNA confirmatory testing in the intervention versus the control groups. The number and proportion of HCV RNA-positive individuals who begin treatment in the intervention versus the control groups. The completion of the Likert scale rankings of ease of use that the participant report regarding the HCV testing process. The cost per test completed and the cost per person diagnosed (serology, RNA) in the intervention versus the control groups.

#### Participant timeline {13}

The participant timeline is presented in Table 1.

**Table 1 Tab1:** Participant timeline

Procedure	Enrolment	Test results	Follow-up #1	Follow-up #2
	Day 0	Weeks 2–4	Weeks 2–4	Weeks 4–8
Inclusion and exclusion criteria via the online survey	X			
Informed consent via the online form	X			
Demographic information; Knowledge, Attitudes and Practices (KAP) survey; risk behaviour via the online survey	X			
Completion of follow-up survey #1 regarding the perceptions of testing processes, uploading of test results, KAP and further linkage to care (if applicable)		X	X	
Completion of follow-up survey #2 regarding the risk behaviours and further linkage to care (if applicable)				X
Linking of data of RNA test results and treatment initiation (if applicable)			X	X
Adverse events/severe adverse events/social harms review	X	X	X	X
Cost data collection/analysis	X	X	X	X

#### Sample size {14}

The study will enrol a minimum of 750 participants who meet the inclusion criteria. There will be a minimum of 250 participants who receive an oral fluid-based HCV self-test, 250 participants who receive a blood-based HCV self-test and 250 participants in the control group. The study is powered to detect at least a 20% between-group difference in HCV antibody self-testing between the intervention group and the control group, based on 80% statistical power and an alpha level of 0.05. As this study is one of the first to explore the impact of an HCV self-testing distribution model, there are no references available to draw on for the expected difference in between-group uptake of antibody testing rates. The use of a 20% between-group difference in HCV antibody testing uptake is based on expert opinion, according to previous experiences with HIV self-testing and the increases in the uptake of testing seen with the use of HIV self-testing [15].

For the primary objective, the null hypothesis is that there is no significant difference in the proportion of individuals reporting HCV test results in the intervention versus control groups. The alternative hypothesis is that home-based HCV self-testing in the intervention group will significantly increase the proportion of individuals reporting HCV test results.

The study is not powered to detect significant differences in the secondary objectives. However, similarly to the primary objective, the null hypothesis would be no significant difference between the intervention versus control groups, with the alternative hypothesis being that home-based HCV self-testing will result in significantly higher numbers of HCV-infected individuals being diagnosed, linked to care and treated, making it a cost-effective approach to HCV case-finding and elimination.

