## Statistical methods

### Statistical methods for primary and secondary outcomes {20a}

Data will be analysed using R (version 4.1 or higher). A summary of the statistical analyses that will be completed by the endpoint is shown in Table 2. These analyses will be conducted among the group of participants who received the oral fluid-based HCV self-test with the control group and the group of participants who received the blood-based HCV self-test with the control group.

**Table 2 Tab2:** Statistical analyses to be completed by the endpoint

Endpoint	Statistical analysis methods
1.1 The number and the proportion of participants who report completing the HCV antibody testing in the intervention group 1.2 To assess whether the proportion of participants who report completing the HCV antibody testing in the intervention group is greater than that reported by the participants in the control group by a margin of 20%	Descriptive statistics: Calculation of proportions with 95% CI of the difference in proportions will be evaluated by using the R function prop.test from the “stats” package, which relies on Wilson’s score method. Test of proportions: Two-sided test with a margin of 20%, implemented with the R function “stats::prop.test” with the following hypotheses: *H*_0_: *p*_fo,*I*_ − *p*_fo,*C*_ ≤ 20% *H*_A_: *p*_fo,*I*_ − *p*_fo,*C*_ > 20% where proportions are defined as *p*_*x*,*y*_ [*x* = investigated outcome (fo, pt, ref, trt), *y* = element of {intervention, control}]) comparing the proportion of individuals reporting HCV test results in the intervention versus control groups and between intervention groups. The differences will be reported together with their confidence intervals and the *p*-value related to the statistical comparison mentioned above. The alpha level will be set at 0.025 (2 two-sided tests with an alpha level of 0.05, with the application of Bonferroni correction).
2.1 Number and proportion of HCV antibody-positive individuals made aware of their status in the intervention versus the control group	Descriptive statistics: Statistical testing comparing the numbers of individuals in the intervention versus control groups and between the intervention groups. For details, see the methodology described for endpoint 1.2.
2.2 Number and proportion of HCV antibody-positive individuals who are referred for and complete HCV RNA confirmatory testing in the intervention versus control group	

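### The stated 80% power at alpha 0.05 belongs to neither analysis in Table 2, and the test family and interval level there do not match the Bonferroni correction

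*Protocol article*

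**What the plan says.** **Sample size {14}.** "The study will enrol a minimum of 750 participants who meet the inclusion criteria": 250 with the oral-fluid kit, 250 with the blood kit and 250 controls. The study is described as "powered to detect at least a 20% between-group difference in HCV antibody self-testing between the intervention group and the control group". The error rates behind that claim are given in the words "based on 80% statistical power and an alpha level of 0.05". For the primary objective, "the null hypothesis is that there is no significant difference in the proportion of individuals reporting HCV test results". The section gives no control-arm uptake and no allowance for non-response.

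**Trial design {8}.** "The participant allocation ratio will be 2:1", so each kit against control is 1:1.

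**Statistical methods {20a}.** The text above Table 2 names two comparisons, each kit against control. The endpoint 1.2 row states a null that the difference is at most 20 points, and applies the test "in the intervention versus control groups and between intervention groups". It adds: "The alpha level will be set at 0.025 (2 two-sided tests with an alpha level of 0.05, with the application of Bonferroni correction". The interval level is given as "Calculation of proportions with 95% CI of the difference in proportions". The primary outcome in Outcomes {12} also uses the 20-point margin.

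**The concern.** Power, alpha, null hypothesis, number of comparisons and confidence level should all describe one analysis. Here the sizing uses one contrast, alpha 0.05 and a zero null. The analysis uses kit-specific contrasts, alpha 0.025 and a 20-point margin.

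Three things are at stake. A reader cannot tell what difference the trial can detect or check why 750 people are enrolled. It is unclear which tests the 5% error rate covers. And a 95% interval may exclude the null value when the test at 0.025 does not reject.

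**Working it through.** **Inputs.** From the documents: 250 per group, a 20-point difference, 80% power, alpha 0.05 (sizing) and 0.025 (testing), nulls of zero and 20 points. Assumption: control uptake is not stated, so it is varied from 5% to 75%. The least favourable case is 40% versus 60%.

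**1. The plan's own figure (zero null, alpha 0.05, 1:1).** With p̄ the mean of the two proportions,

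n per group = [z(1−α/2)·√(2p̄(1−p̄)) + z(0.80)·√(pC(1−pC) + pI(1−pI))]² / Δ²

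For 40% versus 60%: [1.960 × 0.7071 + 0.8416 × 0.6928]² / 0.04 = (1.969)² / 0.04 = 96.9, so 97. Every other control rate needs fewer. Variants do not reach 250 either: 107 with a continuity correction, 77 one-sided, 73 controls plus 146 intervention at 2:1. **The stated combination is not reproduced.**

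**2. Zero null at the alpha actually used (0.025).** For 40% versus 60%: [2.2414 × 0.7071 + 0.5831]² / 0.04 = (2.168)² / 0.04 = 117.5, so 118 per group (128 with a continuity correction).

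Power with 250 versus 250 = Φ{[Δ√n − z(1−α/2)·√(2p̄(1−p̄))] / √(pC(1−pC) + pI(1−pI))}

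= Φ[(3.162 − 1.585) / 0.693] = Φ(2.28) = 98.9%.

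| Control → intervention | n per group for 80%, α 0.05 | n per group for 80%, α 0.025 | Power, 250 vs 250, α 0.05 | Power, 250 vs 250, α 0.025 |
|---|---|---|---|---|
| 10% → 30% | 62 | 75 | 99.99% | 99.97% |
| 20% → 40% | 82 | 99 | 99.9% | 99.7% |
| 40% → 60% | 97 | 118 | 99.5% | 98.9% |
| 60% → 80% | 82 | 99 | 99.9% | 99.7% |

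The difference detectable with 80% power at 250 versus 250 and alpha 0.025 runs from 9.8 points (control 10%) to 13.75 points (control 40% to 45%).

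**3. The 20-point margin.** Power = Φ[(Δ − 0.20)/SE − z(1−α/2)], with SE² = [pC(1−pC) + pI(1−pI)]/250.

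- True difference 20 points: Φ(−2.2414) = 1.25% at two-sided 0.025. This is the tail in the direction of the alternative. At two-sided 0.05 it is 2.5%.
- True difference 30 points, control 30%: SE = √(0.45/250) = 0.0424, so Φ(2.357 − 2.241) = 54.6%.
- 80% power needs a true difference of about 31 to 33 points (control 10% to 40%).

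**4. Number of tests.** Oral–control, blood–control and oral–blood make three. At 0.025 each:

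| Calculation | Two kit-versus-control tests | All three |
|---|---|---|
| Bonferroni bound | 5.0% | 7.5% |
| Simulated, zero nulls, no continuity correction (uptake 30%, 50%) | 4.7%, 4.3% | 6.4%, 5.9–6.0% |
| Simulated, zero nulls, prop.test's default continuity correction | 3.7%, 3.5% | 5.1%, 4.8% |
| Simulated, both kits exactly 20 points above control, margin test (control 30%, 40%) | 2.6%, 2.8–2.9% | 5.0%, 5.0% |

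Simulations used 400,000 trials with 250 per group. In the last row only rejections above the margin count for kit versus control, and oral versus blood is tested against zero in either direction.

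**5. Interval level.** A two-sided test at 0.025 corresponds to a 97.5% interval. For p between 0.025 and 0.05 the 95% interval excludes the null value and the test does not reject. The matching interval is wider by 2.2414/1.9600 = 1.14, about 14%.

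**The case against.** **The two alphas may be one.** The 0.05 could be the overall level that Table 2 then splits. That is a natural reading of Table 2, but the sample size section ties 0.05 to a single contrast and mentions no split. Under a zero null nothing turns on it, since power exceeds 98% either way.

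**250 may contain an allowance.** It is called a minimum, the outcome comes from online follow-up surveys, and an article may leave attrition assumptions to the full protocol. This stands in part: the surplus is unexplained, not shown to be an error. But for non-response alone to bring 250 down to 80% power, at least 1 − 118/250 = 53% of each group would have to contribute nothing at alpha 0.025 (1 − 97/250 = 61% at 0.05). The article does not hint at that.

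**The family may be two.** The text above Table 2 and the primary outcome concern kit or intervention against control only. If oral versus blood lies outside the family, 0.025 is correct. The endpoint 1.2 row nevertheless puts that contrast under the same formal test.

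**95% intervals beside adjusted tests are common,** and the 95% level appears under descriptive statistics. That makes the interval point minor, but the mismatch remains.

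**Stronger readings to resist.** A reader might infer that the trial is too small; against a zero null it is not. A reader might infer that the family-wise error clearly exceeds 5%; that holds only for zero-null tests without continuity correction, and by about one point. A reader might simply replace 80% by 99%; that would be false for the margin test that Table 2 specifies.

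**Conclusion.** The point holds as an inconsistency in the stated design figures. The 80% claim matches neither candidate analysis: power for 20 points is at least 98.9% with a zero null and about 1.25% against the 20-point margin, both at 250 versus 250 and two-sided 0.025. The first figure holds for any control rate, and the second does not depend on it. Both assume that all 250 per group contribute outcomes.

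The family and interval mismatches are real but modest: a 7.5% bound, about 5% to 6% in simulation, and intervals about 14% too narrow for the decision level. The conflict between the two nulls has by far the largest effect and must be settled first, because no power figure can be stated until it is.

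**What to change.** 1. **Reconcile the null.** Sample size {14} uses zero; Outcomes {12} and Table 2 use a 20-point margin. State one throughout.
2. **Restate the sample size for the analysis made:** 250 per kit versus 250 controls, two-sided alpha 0.025, the assumed control uptake, and any non-response allowance. If the null is zero, give about 99% power for 20 points and 80% for about 10 to 14 points. If the margin is kept, say that 80% power needs a true difference of about 31 to 33 points.
3. **Define the family:** two kit-versus-control tests at 0.025 each, with oral versus blood descriptive.
4. **Report 97.5% intervals** for the two confirmatory contrasts.

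The cost is text and somewhat wider intervals. These corrections need no change in enrolment or data collection.

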2.3 Number and proportion of HCV RNA-positive individuals who begin treatment in the intervention versus the control group	
2.4 Analysis of survey responses using proportions and means	Descriptive statistics for survey responses (e.g. proportions, means), as appropriate for the type of response.
2.5 Cost per test completed and cost per person diagnosed (serology, RNA) in the intervention versus control groups	Ingredients-based cost calculation approach.

In a sensitivity analysis, a possible confounding in terms of the time of proband’s actions will be evaluated by analysing the proportions as events by means of Kaplan-Meier analyses with the advantage that dropouts are taken into account as censored values in addition.

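### The secondary hypothesis infers cost-effectiveness from more diagnoses, but the planned average costs per arm cannot support that inference

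*Protocol article*

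**What the plan says.** Sample size {14} gives the alternative hypothesis for the secondary objectives: self-testing is expected to produce "significantly higher numbers of HCV-infected individuals being diagnosed, linked to care and treated, making it a cost-effective approach to HCV case-finding and elimination". The same paragraph opens by saying that the study has no designed power for the secondary objectives.

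The economic objective in Objectives {7} is narrower: a comparison of the cost of self-testing with that of standard care. Outcomes {12} and Table 2, endpoint 2.5, define the measure as "Cost per test completed and cost per person diagnosed (serology, RNA) in the intervention versus control groups". Table 2 names an ingredients-based costing as the method. Under Plans for assessment and collection of outcomes {18a}, costs come from a desk review of what the study spent, from the provider's perspective. Methods for additional analyses {20b} plans nothing further.

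On numbers, the protocol sets minimum group sizes, including "250 participants who receive a blood-based HCV self-test and 250 participants in the control group". The only prevalence is in Background and rationale {6a}: "Malaysia has an estimated HCV prevalence of 1.9% among its adult population". That section attributes the figure to an opt-in screening campaign. It adds that the groups the platform serves may be at higher risk and that estimates for them are limited.

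**The concern.** Finding more infected people does not by itself make a programme cost-effective. The extra cost has to be set against the extra effect. The two planned measures divide each arm's cost by that arm's own yield, so they describe each arm separately. A referral arm that tests few people cheaply can look better per test than an arm that tests many more, and neither average gives the price of the additional people reached.

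The second measure has a further weakness. Its denominator is the number of positives observed in the arm, which may be very small among controls. If it is zero, the ratio is undefined.

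The protocol says the findings will inform the health ministry on scale-up. A cost-effectiveness statement written in as the expected result, next to an unstable cost per diagnosis, could carry more weight in that decision than the data allow.

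**Working it through.** **1. Plan's own figure.** There is none to reproduce. The protocol gives no expected number of diagnoses, no control uptake and no cost. The one quantity it is sized for is uptake ("The study is powered to detect at least a 20% between-group difference in HCV antibody self-testing"), and nothing below depends on whether that calculation is right.

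**2. Averages against the incremental ratio.** Let *u* be uptake and *a* the average cost per test completed in an arm. Cost per randomised participant is *u* × *a*. Incremental cost per additional person tested is

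(*u*_I × *a*_I − *u*_C × *a*_C) / (*u*_I − *u*_C).

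With invented figures, suppose 75 of 250 controls test for 750 units (10 per test) and 150 of 250 self-testers test for 3,000 units (20 per test). Cost per randomised participant is 3 and 12, and the uptake difference is 0.30. The ratio is (12 − 3)/0.30 = 30 units per additional person tested, which is neither 10 nor 20.

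**3. Expected control antibody positives.** Inputs: 250 controls (Sample size {14}); prevalence 1.9% (Background {6a}), with 0.5% to 10% as an assumed range for the trial population; control uptake 20% to 60%, assumed. Expected positives = 250 × uptake × prevalence. Chance of none = (1 − uptake × prevalence)^250.

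| Prevalence | Uptake 20% | Uptake 40% | Uptake 60% |
|---|---|---|---|
| 0.5% | 0.25 (78%) | 0.50 (61%) | 0.75 (47%) |
| 1.9% | 0.95 (39%) | 1.90 (15%) | 2.85 (6%) |
| 5% | 2.5 (8%) | 5.0 (0.6%) | 7.5 (<0.1%) |
| 10% | 5.0 (0.6%) | 10.0 (<0.1%) | 15.0 (<0.1%) |

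Each cell shows the expected count, with the chance of zero in brackets.

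If 70% of antibody positives are RNA-positive (assumed), the 1.9% row falls to 0.67–2.0, with a 51% to 14% chance of none. With uptake 20 points higher under self-testing, each kit group of 250 expects 250 × (0.40 to 0.80) × 0.019 = 1.9 to 3.8 positives, and the pooled 500 expect 3.8 to 7.6.

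**4. Effect on cost per person diagnosed.** Exact Poisson 95% intervals for the count:

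- count of 1: 0.025 to 5.57, about 220-fold
- count of 2: 0.242 to 7.22, about 30-fold
- count of 3: 0.619 to 8.77, about 14-fold

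The part of the ratio driven by the count has the same spread. At 5% prevalence the coefficient of variation is still 1/√2.5 = 63% to 1/√7.5 = 37%.

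**5. Contrast with the uptake difference.** Take uptake of 30% and 50% (assumed) in 250 controls and one kit group of 250. The standard error is √(0.30 × 0.70/250 + 0.50 × 0.50/250) = √(0.00084 + 0.00100) = 0.043. The 95% interval is 0.20 ± 0.084, or 0.116 to 0.284, a spread of about 2.4-fold. That is the denominator of the incremental ratio.

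**6. The premise of more diagnoses.** For the proportion diagnosed among all randomised, with the same 20-point uptake gain and a test against zero difference, approximate power is 5% to 8% at 1.9% prevalence and 14% to 28% at 10%. This agrees with the protocol's own statement that these objectives are unpowered.

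**The case against.** The strongest reply is that this is one loose clause. It sits in an alternative hypothesis, beside an explicit disclaimer of power, and the formal objective is only to compare costs. Much of this stands, and several stronger readings should be set aside.

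- A reader might infer that the trial would declare self-testing cost-effective. The document contains no cost test, threshold or decision rule from which that could happen.
- A reader might take one to three control diagnoses as a property of the design. It depends on a general adult prevalence and an assumed uptake. Key populations may be at higher risk, known positives are excluded, and 250 is a minimum.
- A reader might say that the randomised uptake result plays no part in the costs. It does: cost per test completed divides by tests completed, which is arm size times uptake. That measure also does not suffer from few positives, so the instability affects only cost per person diagnosed.
- A reader might call the economic methods missing. An article condenses its protocol, and intervals or sensitivity analyses may be set out in the full document. Their absence here is not the point.

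The inference as written is not answered by this. A fuller document can add methods, but it does not make more diagnoses equivalent to cost-effectiveness. The incremental ratio can be formed from arm costs, arm sizes and uptake, all of which will be available, but the economic outcomes as stated do not include it.

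**Conclusion.** The concern holds in a limited form. The hypothesis states a conclusion that the two stated economic outcomes cannot deliver, because neither gives the cost of the additional people reached. This needs no assumption about prevalence or uptake.

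The instability of the control cost per person diagnosed is likely but conditional. It rests on 250 controls, uptake of 20% to 60% and the 1.9% adult prevalence. Over 0.5% to 10% prevalence, the expected control count runs from about 0.25 to 15, so at the upper end the ratio would be imprecise but not undefined. The primary analysis is unaffected, and the documents do not show that a false claim of cost-effectiveness would follow.

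**What to change.** - Delete the cost-effectiveness clause from the secondary alternative hypothesis, and limit the economic part to a comparison of costs, as the objective already does.
- Add incremental cost per additional person tested: the difference in cost per randomised participant divided by the randomised difference in uptake. Give it an interval reflecting uncertainty in uptake, and a deterministic sensitivity analysis on the desk-review unit costs. No participant-level costs are described, so resampling participants would capture variation in uptake only.
- Report the observed cost per person diagnosed in each arm as descriptive, with the number of positives and its exact interval, and state beforehand that a zero count will be shown as not estimable.
- If cost per diagnosis is also calculated from positivity pooled over arms, label it a sensitivity analysis. It assumes that testers in both arms have the same HCV risk, whereas reaching people whom facility services miss is part of the study's purpose. The baseline survey can check measured risk factors but not positivity itself.

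The cost is an edit to one sentence and a short extra calculation, with no new data collection.
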